Observational studies have shown that adequate sleep is associated with lower body mass index (BMI) and a reduced risk of excess weight [4,26]. Experimental studies further demonstrate that sleep restriction decreases physical activity and increases sedentary behavior [[15], [16], [17]], despite higher recorded activity counts due to increased wakefulness [27,28]. Clinical trials focused on sleep hygiene—such as maintaining consistent sleep schedules—have shown benefits including increased physical activity [29,30], reduced sedentary behavior [31], and improved dietary habits [32]. These trials also highlight the role of sleep in weight and fat mass loss [33,34], although findings are mixed, with some studies reporting limited effects on weight-related outcomes [35]. While these findings suggest that improving sleep could aid in weight management and reduce related chronic conditions within the AA community, most tailored sleep interventions focus primarily on sleep apnea [36,37] leaving a gap in research on behavioral sleep interventions [[38], [39], [40]]. It is important to note that while a recent meta-analysis found limited evidence for consistent bidirectional associations, analyses included only observational studies and exercise interventions without considering sleep interventions [41].

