Progressive Missionary Baptist Church, led by co-author MM, has served the St. Paul community since 1992 and is widely recognized for its commitment to health equity and community engagement. With a predominantly Black/African American congregation of over 400 members, the church is affiliated with the Minnesota State Baptist Convention and the National Baptist Convention. Its ministry encompasses a range of programs, including youth development, discipleship, and pastoral care. The church holds weekly Sunday services in both virtual and in-person formats, with additional Bible studies and community activities occurring throughout the week. These services are recorded and broadcast online, further extending the church's outreach. Progressive Missionary Baptist Church has a history of engagement in health research and public health initiatives. At its initial outset, recruitment will be limited to congregation members.

**Recruitment and Eligibility Criteria.** The inclusion and exclusion criteria will be consistent across both Phases 1 and 2. The inclusion criteria are as follows: average habitual sleep duration of ≤6 h per night, not meet Physical Activity Guidelines for leisure physical activity (<150 min of moderate/vigorous activity or <75 min of vigorous activity), 21–75 years of age, Body Mass Index (BMI) > 25.0 kg/m^2^, and self-identify as Black or African American. Exclusion criteria include self-reported organ-related disorders such as COPD, cardiac arrhythmia, or gastro-esophageal disorder; being pregnant or less than four months postpartum; and having an infant under one year old living in the household.

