## Phase 2: intervention, adaptation, implementation, and Analytic Plan (n = 80)

4

During Phase 2, we will complete Aim 2a and 2b of the study, which focuses on exploring the feasibility, satisfaction, and plausibility (i.e., preliminary efficacy) of a sleep intervention designed to increase sleep duration and physical activity (PA). This phase employs a 6-week randomized controlled trial (RCT) to evaluate the intervention compared to a contact control group (see Fig. 1). Phase 2 involves a 7-day baseline assessment, followed by a 4-week intervention period, and concluding with a 7-day follow-up assessment. Eligible participants will be randomly assigned to one of two conditions: a sleep extension intervention or contact control. The primary goal of the sleep intervention is to increase sleep duration by 1 h over the course of four weeks and improve PA.

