**Fig. 1 fig1:**
[figure not shown]
Aim 2 sleep intervention randomized control trial design. *∗*Measurement of metabolic (insulin, adiponectin, leptin) and pro-inflammatory (IL-6, CRP, TNF-α).

**Interventions.** The sleep extension intervention is designed for AA adults who habitually obtain insufficient sleep, regardless of sleep disorder status, and aims to increase nightly sleep duration and daily physical activity. While sleep duration is a primary target for preliminary efficacy, we include physical activity based on prior research indicating the reciprocal relationship between sleep and physical activity (see *Introduction*). The intervention adapts selected components of Cognitive Behavioral Therapy for Insomnia (CBT-I) [79], including psychoeducation and stimulus control, while intentionally excluding sleep restriction. Participants receive four weekly one-on-one sessions via Zoom, delivered by trained study staff following a standardized protocol. Interventionists include master's-level counseling psychology graduate students trained in behavioral sleep principles and community engagement. Sessions follow a structured framework. Session 1 (60 min) introduces foundational sleep health concepts, including psychoeducation on the physiological and cognitive impacts of insufficient sleep, relaxation training, and individualized goal setting for bedtime extension. Sessions 2–4 (30 min each) involve review of weekly sleep diaries, monitoring of adherence to incremental bedtime targets (e.g., 15-min weekly increases), identification of barriers, and reinforcement of sleep-promoting behaviors such as consistent wake times and reduced evening screen use. Culturally relevant strategies—such as faith-based wind-down routines and household sleep negotiations—are integrated based on participant context. Tailored home practice recommendations, including relaxation exercises, are also provided weekly. Participants are encouraged to maintain their extended sleep schedule during the follow-up week. The intervention does not include any content related to physical activity promotion or goal-setting. However, physical activity is assessed as a secondary, non-targeted behavioral outcome to examine whether increasing sleep duration may be associated with incidental changes in activity levels.

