*Primary Outcomes.* Primary outcomes include feasibility and satisfaction of the culturally adapted sleep extension intervention. Feasibility will be determined by achieving an average intervention adherence rate of at least 75 % among participants in the sleep intervention group. That is, feasibility is achieved if participants attend an average of at least 3 out of 4 sessions. Adherence is operationalized as the proportion of sessions attended per participant, averaged across all participants in the intervention group. The adherence rate is the proportion of sessions attended per participant, averaged across the intervention group. Satisfaction will be assessed through participant interviews and the Client Satisfaction Questionnaire [92] that measures how well the intervention met the participants' needs, perceived improvement in skills, and likelihood of recommending intervention to others). Higher scores indicate greater satisfaction with the intervention, and satisfaction will be met if average scores across participants is ≥ 20.

*Secondary outcomes.* Secondary outcomes include objective and subjective measures of physical activity and sleep, as well as cancer risk-related biomarkers pre- and post-intervention. Although the intervention does not directly target physical activity, we assess PA to explore whether increasing sleep duration may yield subsequent changes in movement patterns. Self-reported physical activity levels will be assessed with the 7-item International Physical Activity Questionnaire – Short (IPAQ-SH) [93], and sedentary behavior will be assessed using a single-item measure of sitting used in National Health and Nutrition Examination Survey (NHANES). Self-reported sleep duration and quality will be measured using the 19-item Pittsburgh Sleep Quality Index (PSQI) [74], and the 9-item Consensus Sleep Diary [94]. Objectively measured PA and sleep duration and quality will be measured using wrist-worn actigraphy on the non-dominant hand for 1-week pre/post-intervention. *Exploratory biomarker* outcomes (n = 20) include pro-inflammatory markers (IL-6, TNF-α, CRP) and metabolic indicators (insulin, glucose, adiponectin), and blood pressure.

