**Analytic plan.** Quantitative data from Phase 2 will be analyzed to assess feasibility, acceptability, and preliminary efficacy. Descriptive statistics, including means, medians, standard deviations, and 95 % confidence intervals (CIs), will be reported for sleep and PA outcomes. Pre-post changes will be examined for ceiling or floor effects and range restrictions. Graphs will visualize outcome distributions over time by group, highlighting differences in demographics and retention status.

While the power analysis was originally conducted for a repeated measures ANOVA, the primary analytic approach will use linear mixed models (LMMs) to account for repeated measurements and missing data. Given the exploratory nature of this pilot study, p-values will not be reported. Instead, standardized effect sizes (e.g., Cohen's d for between-group differences, standardized β coefficients from LMMs) will be reported with their standard deviations and 95 % CIs to evaluate trends and inform future trials.

LMMs will be used to examine within-group and between-group changes in primary outcomes (sleep quality, sleep duration, PA, and sedentary behavior) over the 4-week study period. While group differences over time will be explored, this study is not powered to detect interaction effects with high precision. Therefore, results will focus on descriptive effect size estimates rather than hypothesis-driven interaction testing. Analyses will follow the intention-to-treat (ITT) principle, ensuring that all randomized participants are included in analyses regardless of adherence. Missing covariate data will be handled via multiple imputation, while missing outcome data will be addressed using maximum likelihood estimation (MLE) within the LMMs. Baseline differences in participant characteristics and outcomes will be examined, with significant differences included as covariates to control for potential confounding. Loss to follow-up rates and differential attrition effects will also be evaluated.

For exploratory Aim 2b, changes in inflammatory and metabolic biomarkers (or their log transformations, if needed) will be described using means, standard deviations, and 95 % CIs to identify trends in proinflammatory and metabolic markers.

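### The sitting item, and any actigraphy total that scales with time awake, mixes the shorter waking day caused by sleep extension with change in movement behaviour, and should also be reported relative to waking time

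*Protocol article*

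**What the plan says.** Section 4 (Phase 2) sets the intervention goal: to "increase sleep duration by 1 h over the course of four weeks", in people whose eligibility requires "average habitual sleep duration of ≤6 h per night" (Methods, Recruitment and Eligibility Criteria). Under Interventions, bedtimes are extended in small steps (for example "15-min weekly increases"), with "reinforcement of sleep-promoting behaviors such as consistent wake times and reduced evening screen use". The sessions contain no activity content. Activity is measured "to examine whether increasing sleep duration may be associated with incidental changes in activity levels".

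Under Measures, Secondary outcomes, "sedentary behavior will be assessed using a single-item measure of sitting used in National Health and Nutrition Examination Survey (NHANES". Self-reported activity comes from the short IPAQ. Objective activity comes from one week of wrist actigraphy before and after the intervention, with no metric named. A sleep diary is also collected.

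The Analytic plan says that "LMMs will be used to examine within-group and between-group changes in primary outcomes (sleep quality, sleep duration, PA, and sedentary behavior" and reports standardised effect sizes with confidence intervals, without p-values, to inform later trials. Nothing there refers to waking time. The Introduction does recognise the link: it says that sleep restriction lowers physical activity "despite higher recorded activity counts due to increased wakefulness".

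**The concern.** The stated question concerns behaviour: whether people who sleep more also move differently. Sitting time (read here as time per day, since the item is not reproduced) also depends on how many hours a person is awake, and the intervention is designed to reduce those hours. If it works, some sitting is replaced by sleep even if nobody changes what they do while awake. Randomisation does not remove this, because the shorter day is a consequence of assignment, and it grows with the success of the intervention. The Introduction describes the same mechanism in reverse for recorded counts, but the caveat is not carried into the outcomes.

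At stake is interpretation. A fall in sitting could be read as less sedentary behaviour when part or all of it is extra sleep, and the resulting effect size would be passed to the next trial. If actigraphy is summarised as a daily total, the same mechanism would work against an activity benefit.

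**Working it through.** The article gives no figure for this point, so there is none to reproduce. The check is a time budget.

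**Inputs from the article.** Target gain 1 h; four steps of 15 min give 60 min, which agrees. Baseline sleep of 6 h or less, so a waking day of at least 24 − 6 = 18 h. Moderate-to-vigorous activity below 150 min at entry; the criterion gives no period and is taken as weekly.

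**Assumptions, not in the article.** Sitting of 6–10 h/day, or alternatively 40–70% of waking time; between-person SD of sitting 120–240 min/day; the 1 h gain fully achieved.

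**1. Waking time lost** = gain / waking day.
- From 6 h sleep: 1/18 = 5.6%.
- From 5 h sleep: 1/19 = 5.3%.

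**2. Sitting displaced with behaviour per waking hour unchanged** = sitting share × 60 min.
- 6 h sitting: 6/18 × 60 = 20 min/day; 10 h: 10/18 × 60 = 33 min/day.
- 40%: 24 min/day; 70%: 42 min/day.
- Limits: 60 min/day if the lost hour was all sitting, 0 if none of it was.

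**3. On the standardised scale** = minutes / SD.
- Proportional loss: 20/240 = 0.08 to 42/120 = 0.35.
- All-sitting limit: 60/240 = 0.25 to 60/120 = 0.50.

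**4. Activity.**
- A total-count metric, if used, falls by 5.6% if the lost hour was as active as the average waking hour, and by less if it was quieter.
- Moderate-to-vigorous minutes under proportional loss: 149/18 = about 8 min/week at most, and 0 if none took place in that hour.

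**5. Smaller gain.** At 0.5 h: 0.5/18 = 2.8% of waking time, sitting 10–21 min/day, limit 30 min/day.

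**6. What a waking-time ratio does.**
- Proportional loss: the sitting share is unchanged, so the displacement is removed.
- Lost hour all sitting, from 10 h: 10/18 = 55.6% becomes 9/17 = 52.9%. At the old share, 17 h awake would hold 10/18 × 17 = 9.44 h of sitting, so 0.44 h (about 27 min) of the 60 min remains in the ratio.
- Same case, activity total unchanged: activity per waking hour rises by 18/17 − 1 = 5.9% although nobody moved more.

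The ratio therefore reduces the problem for sitting but does not abolish it, and for activity it can create an apparent gain.

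**The case against.** The strongest reply has five parts.

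- **The actigraphy metric is not stated.** A reader might infer that total counts will be analysed and will fall. The article does not say so, and a condensed article may leave the metric to a fuller document. This stands: the point about counts is conditional.
- **The activity question is not lost.** A reader might infer that these outcomes cannot answer it. That is not supported. Moderate-to-vigorous minutes are barely touched, IPAQ activity is little affected, and a rise in a total despite a shorter day would be informative.
- **Less total sitting is a genuine randomised effect.** This also stands. Only its reading as changed waking behaviour is open. Nor must sitting fall: the article does not say what the lost hour contained, and reduced screen use is only one of its examples.
- **The extremes do not occur together.** The 60 min limit needs the lost hour to be all sitting, while the 5.6% count loss needs it to be as active as average.
- **The ratio has its own artefact, and the stakes are modest.** Both are true. The denominator is itself changed by the intervention, so ratios should not replace totals. With 80 × (1 − 0.125) = 70 completers, 35 per arm, the 95% interval for an unadjusted standardised difference is about ±1.96 × √(2/35) = ±0.47, comparable to the largest displacement effect.

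What remains is the sitting item. The article chooses that measure and commits sedentary behaviour to the model, so this limb does not rest on silence about a metric. A wide interval is also no reason to leave a foreseeable shift in the point estimate unexplained.

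**Conclusion.** The point holds in a limited form. The sitting item, and any actigraphy total that scales with time awake, combines a shorter waking day with movement behaviour, and the article provides nothing to separate them. With the full 1 h gain from 6 h sleep, waking time falls 5.6% and sitting about 20–42 min/day without any change per waking hour, within limits of 0 and 60. The waking-time figure follows from the article. The minutes rest on assumed sitting levels, and the standardised values (about 0.1–0.35, up to 0.5 at the limit) on assumed SDs as well. All scale with the gain actually achieved. The documents do not support saying that the activity outcomes are uninformative, that counts will fall, or that raw totals are invalid. This is an inexpensive improvement to reporting and interpretation; it does not undermine the design.

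**What to change.** In Secondary outcomes and the Analytic plan:

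1. Report sitting as a share of waking time (24 h minus diary or actigraphy sleep, with the source fixed in advance) beside raw sitting hours.
2. Name the actigraphy activity metric. If it is a total that scales with waking time, report it per waking hour as well.
3. Keep raw totals, including moderate-to-vigorous minutes, as effects of assignment.
4. State that raw totals include displacement by sleep, and that the ratios are not free of it when the lost hour was mainly sitting.
5. Claim a behavioural change in sedentary time or activity only when both versions agree and the change exceeds what displacement alone would produce. For sitting, displacement cannot exceed the between-arm gain in sleep, so the raw fall can be compared directly with that gain. For an activity benefit, the raw total should rise as well as the rate.

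The diary and actigraphy already supply the denominator. The cost is some wording and a second derived measure that is slightly harder to read.

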**Analytic plan.** Quantitative data from Phase 2 will be analyzed to assess feasibility, acceptability, and preliminary efficacy. Descriptive statistics, including means, medians, standard deviations, and 95 % confidence intervals (CIs), will be reported for sleep and PA outcomes. Pre-post changes will be examined for ceiling or floor effects and range restrictions. Graphs will visualize outcome distributions over time by group, highlighting differences in demographics and retention status.

While the power analysis was originally conducted for a repeated measures ANOVA, the primary analytic approach will use linear mixed models (LMMs) to account for repeated measurements and missing data. Given the exploratory nature of this pilot study, p-values will not be reported. Instead, standardized effect sizes (e.g., Cohen's d for between-group differences, standardized β coefficients from LMMs) will be reported with their standard deviations and 95 % CIs to evaluate trends and inform future trials.

LMMs will be used to examine within-group and between-group changes in primary outcomes (sleep quality, sleep duration, PA, and sedentary behavior) over the 4-week study period. While group differences over time will be explored, this study is not powered to detect interaction effects with high precision. Therefore, results will focus on descriptive effect size estimates rather than hypothesis-driven interaction testing. Analyses will follow the intention-to-treat (ITT) principle, ensuring that all randomized participants are included in analyses regardless of adherence. Missing covariate data will be handled via multiple imputation, while missing outcome data will be addressed using maximum likelihood estimation (MLE) within the LMMs. Baseline differences in participant characteristics and outcomes will be examined, with significant differences included as covariates to control for potential confounding. Loss to follow-up rates and differential attrition effects will also be evaluated.

For exploratory Aim 2b, changes in inflammatory and metabolic biomarkers (or their log transformations, if needed) will be described using means, standard deviations, and 95 % CIs to identify trends in proinflammatory and metabolic markers.

## Discussion

5

Project SHINE is a community-based pilot study designed to address significant sleep disparities among Black/African American adults. This study evaluates the feasibility, satisfaction, and plausibility (i.e., preliminary efficacy) of a culturally tailored, virtually delivered sleep intervention aimed at improving sleep duration and physical activity. Although physical activity behaviors were not targeted during the intervention sessions, we measure it as a secondary outcome to assess whether improvements in sleep may indirectly support increased movement. The sleep extension intervention adaptation and pilot feasibility study is structured into two phases. Phase 1 involves qualitative interviews to explore sleep-related social contextual factors and refine the intervention. Phase 2 is a randomized controlled trial comparing the sleep extension intervention to a contact control group. This trial will provide insights into the contextual factors affecting the adoption of behavioral sleep interventions within a church setting and identify barriers and facilitators to implementation. Additionally, it will generate data to estimate effect sizes, informing the design of a future efficacy trial. The findings will contribute to the development of pragmatic community-based behavioral interventions to improve sleep among AA adults.

## Ethics approval and clinical trial registration

The trial was granted full ethics approval by the University of Minnesota Institution Review Board (Reference number STUDY00017901). The trial is registered with ClinicalTrials.gov ID: NCT06226077.

## Data Availability

Data will be made available on request.
